### Endpoints

The primary endpoint is the incidence of postoperative complications (Clavien–Dindo classification grade ≥ III) [35]. The rate of severe postoperative complications in all eligible patients will be investigated, and risk factors affecting them will be determined.

A key secondary endpoint is the incidence of intraoperative vascular injury around the SMV. The rate of intraoperative vascular injury around the surgical trunk in all eligible patients will be investigated, and risk factors affecting it will be extracted.

Other secondary endpoints include the incidence of postoperative complications (Clavien–Dindo classification grade ≥ II), 5-year overall survival, recurrence-free survival, and other short- and long-term outcomes (operative time, blood loss, conversion rate, degree of lymph node dissection, intraoperative complication rate, reoperation rate, R0 resection rate, local recurrence rate in the whole cohort and by stage, and incidence of bowel obstruction and herniated abdominal wall scarring). Factors influencing the above endpoints will be determined for all eligible patients. Furthermore, comparisons will be made between each subgroup, as shown in Table 1.

**Table 1 Tab1:** Secondary endpoints

1. Short-term results by approach (a. Medial approach vs. retroperitoneal approach; b. Medial approach vs. cranial approach; c. Retroperitoneal approach vs. cranial approach; a–c for laparoscopic surgery and robotic surgery, respectively)
2. Short-term results of robot-assisted and laparoscopic surgery (Comparison in all approaches, medial approach, retroperitoneal approach, and in each ASA-PS, respectively)
3. Short-term results by degree of lymph node dissection (D2, D3v, D3a)
4. Long-term results by approach, robot or laparoscopy, and degree of dissection
5. Impact of experience on short-term and long-term outcomes after the surgery performed by the surgeons before obtaining board certification in gastrointestinal surgery (including the investigation by each approach, robot/laparoscopy, and degree of lymph node dissection)
6. Impact of surgeons’ case volume prior to obtaining board certification in gastrointestinal surgery on short- and long-term outcomes following robot-assisted procedures
7. Impact of the participation of Endoscopic Surgical Skill Qualification-certified surgeons in surgery and their role in the procedure on short- and long-term outcomes
8. Impact of anastomosis method on short- and long-term outcomes

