Participating institution backgroundInstitution type and sizePatient backgroundPatient age; sex; body mass index; American Society of Anesthesiologists Physical Status; Eastern Cooperative Oncology Group performance status; albumin level; lymphocyte count; presence of dementia, diabetes, chronic kidney disease, chronic liver disease, or respiratory comorbidities; history of cardiac or cerebrovascular disease; use of steroids/immunomodulators and antithrombotic drugs; preoperative bowel obstruction; preoperative anaemia; abscess or peritonitis; preoperative therapy; history of laparotomy; timing of surgery; primary tumour location; and tumour stage at initial diagnosis (clinical stage, T factor, N factor).Technique and surgeonsWhether the surgeon is a board-certified gastrointestinal surgeon, whether an Endoscopic Surgical Skill Qualification-certified surgeon participates in the operation and his or her role, the approach, blood vessels to be dissected, procedure of dissecting the accessory right colic vein (via the cranial or caudal side), level and direction of lymph node dissection, instruments used during node dissection, method of anastomosis, combined resection of other organs, whether a robot is used, number of previous robotic-assisted right-sided colon resections (ileal resection, right hemicolectomy, or extended right hemicolectomy), and whether a robotic surgery proctor participates in the surgery if robotic surgery is used.Surgical outcomesThe date of surgery, operation time, blood loss, presence of intraoperative vascular injury, other intraoperative complications, 30-day postoperative survival, open conversion, intraoperative blood transfusion, details and grade of postoperative complications within 30 days (Clavien–Dindo classification grade ≥ II), onset and date of intervention for cases with anastomotic leakage/deep wound infection (surgical site infection [SSI]), enforcement and date of reoperation, drain placement, anti-adhesive placement, date of discharge, and operative death.In cases of intraoperative vascular injury:Timing of intraoperative vascular injury; response to intraoperative vascular injury; unplanned bowel resection due to bleeding; open conversion due to bleeding; final post-haemostatic status; and amount of blood transfusion, blood products, and albumin administered from intraoperative to postoperative day 3.Surgical deathsCause of death, date of death, and date of therapeutic intervention.Pathological and histological findings and postoperative courseTumour diameter, histological type (main), pathological stage, T-factor, N-factor, R-status, number of harvested lymph nodes, number of lymph node metastases, presence and details of adjuvant therapy, survival outcome, date of confirmation of final survival outcome, date of confirmation of recurrence, and type of initial recurrence.Patients with pStage 0 and pStage IV will be censored, and no follow-up will be performed after initial postoperative discharge. The development of intestinal obstruction (Clavien–Dindo classification grade ≥ II) and abdominal wall scar hernia will be investigated during follow-up. Patients will be followed up during the postoperative period according to the Japanese Society for Cancer of the Colon and Rectum guideline schedule, and tumour marker levels, thoracoabdominal computed tomography (CT) results, and colonoscopy results will be collected. Omitting observations as part of routine medical care will be deemed acceptable at the discretion of the treating physician [36].

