(23) Final bleeding control: possible/impossible (operative death).(24) Timing of intraoperative vascular injury: during lymph node dissection, mobilisation, intracorporeal anastomosis, extracorporeal anastomosis, and others (described at the time of adhesion dissection, drain insertion, etc.).(25) Other intraoperative complications: list those requiring intraoperative intervention (e.g., injury to other organs).(26) Open conversion: a skin incision ≥ 8 cm is generally defined as an open conversion. However, if the incision exceeds 8 cm solely for the purpose of tumor extraction, it shall not be considered an open conversion.(27) Postoperative complications (within 30 days): Clavien–Dindo classification grade ≥ II should be used.(28) Date of onset of anastomotic leakage/deep SSI: the date of onset is defined as the earliest time of abnormality during the initial physical examination, such as fever, abdominal pain, abnormal discharge from the drainage tube, blood test, and imaging.(29) Treatment intervention date: the date of treatment intervention is defined as the date corresponding to any of the following: administration of medical therapy (in the case of Clavien–Dindo classification grade II); performance of endoscopic, surgical, or interventional radiology (IVR) procedures without general anesthesia (grade IIIa); performance of endoscopic, surgical, or IVR procedures with general anesthesia (grade IIIb); or admission to the intensive care unit (ICU) (grade IV). Additionally, in cases of anastomotic leakage or deep surgical site infection (SSI), the date should be recorded if a new percutaneous drain is inserted or an existing one is replaced.(30) 30-day death: death from any cause within 30 days of surgery.(31) Surgical death: 30-day death or death during hospitalisation 31–90 days postoperatively.(32) Histological type, pathological stage, T and N stages, and R status: according to the Japanese Classification of Colorectal, Appendiceal, and Anal Carcinoma, third English Edition [37].(33) Postoperative adjuvant therapy: indicate whether at least one course has been completed, and specify the type of chemotherapy administered.(34) Recurrence-free survival: duration from the date of first treatment (surgery or start of preoperative therapy) to the date of the last confirmed recurrence-free/recurrence.(35) Local recurrence: local recurrence will be assessed based solely on the initial recurrence, with distinctions made between lymph node recurrence, anastomotic site recurrence, and other locations.(36) Intestinal obstruction during follow-up (Clavien–Dindo classification grade ≥ II): only the first occurrence 30 days after surgery will be considered.(37) Abdominal wall scar hernia: this will be diagnosed based on imaging findings, such as CT, or palpation of the hernia in the surgical scar. Only the first occurrence 30 days after surgery will be considered.

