Secondary endpoints: Summary statistics for patient background and other surgical outcomes will be calculated. A multivariate logistic regression or multiple regression analysis will be performed using the factors listed in the survey items that may influence outcomes. A random-effects model will be used to account for differences between the centres. The main endpoint for short-term outcomes for each subgroup is postoperative complications (Clavien–Dindo classification grade ≥ II), and group comparisons will be conducted after propensity score matching (differences between groups will be tested using Student’s t-test and the χ^2^ test) and logistic regression to identify confounders. Multiple regression analysis will be used to analyse continuous variables. A random-effects model will be used to account for the differences between institutions. The Kaplan–Meier method will be used to plot cumulative late complication curves, local and overall recurrence-free survival curves, and overall survival curves for long-term outcomes. To account for confounding factors, a multivariate Cox regression analysis will be performed using preoperative and postoperative factors that may contribute to recurrence and late complications, and risk factors will be examined. In addition to regression analysis of factors, each factor will be discussed from clinical and medical perspectives to reach a combined perspective.

The number of experienced cases will be added to the factors in the multivariate analysis to examine their effect on the outcome. The correlation of the number of cases experienced and outcomes (operation time and blood loss) with the learning curve will be evaluated using the moving average method and the cumulative sum curve.

Statistical significance will be set at *p* < 0.05.

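### The long-term Cox model adjusts for postoperative factors in the name of confounding control, although several of these factors can be consequences of the technique or surgeon being compared

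*Protocol article*

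**What the plan says.** The secondary-endpoints part of Statistical analysis gives both the purpose and the covariate scope of the long-term model. The purpose is control of confounding; the scope is that "a multivariate Cox regression analysis will be performed using preoperative and postoperative factors that may contribute to recurrence and late complications". The sentence then adds a second aim: "and risk factors will be examined". The same section ties propensity score matching to short-term subgroup outcomes. It also plans logistic and multiple regression for secondary endpoints, but these are not methods for censored follow-up.

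Table 1 lists, as item 4, "Long-term results by approach, robot or laparoscopy, and degree of dissection". Items 5 to 8 extend the long-term question to surgeons not yet board-certified, their case volume in robotic procedures, participation of skill-qualified surgeons, and anastomosis method.

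The section on observation and investigation data shows which postoperative variables are available: "details and grade of postoperative complications within 30 days", "R-status, number of harvested lymph nodes, number of lymph node metastases", and "presence and details of adjuvant therapy". Under Definition of assessment data, item 33 codes adjuvant therapy as follows: "Postoperative adjuvant therapy: indicate whether at least one course has been completed". Item 34 starts recurrence-free survival at first treatment, meaning surgery or the start of preoperative therapy.

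**The concern.** A confounder of a technique comparison must be a cause, or a marker of a cause, of both the choice of technique and the outcome. A complication on day 5 or a positive margin cannot have influenced how the operation was done. It may well have been influenced by it; the Background presents technique and surgeon proficiency as possible determinants of safety. Conditioning on such a variable blocks part of the effect that Table 1 seeks. Where the variable shares unmeasured causes with the outcome, it can also introduce collider bias.

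Degree of dissection has an added problem. Item 19 defines D2, D3v and D3a by how far dissection is carried, and this can change node yield and so pathological N. Adjusting the D-level contrast for pathological N then compares patients within stages whose membership depends on the exposure.

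What is at stake is the reading of the five-year technique and surgeon comparisons. A single model labelled as confounder control invites its technique coefficients to be read as total effects when they are not.

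**Working it through.** The article states no hazard ratio, event count or power for the Cox models, so there is no figure to reproduce. The check is one of logic, with two illustrations. Every rate below is an assumption, apart from the five-year horizon, which is the follow-up stated in the article.

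**1. Classifying the recorded variables**

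| Variable | When determined | Role in a technique contrast |
|---|---|---|
| Age, ASA-PS, ECOG-PS, comorbidity, cT/cN, location, timing of surgery, institution | Before surgery | Possible confounders |
| 30-day complications, R status, node yield | At or after surgery | Possible consequences of technique |
| Pathological N | After surgery | Mostly pre-existing disease, but detection can depend on extent of dissection |
| pT, histological type, tumour diameter | Measured after surgery | Mainly pre-existing disease |
| Adjuvant therapy, at least one course completed | Known only some time after surgery | Post-baseline treatment |

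The plan's wording admits every row as confounder control.

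**2. Adjusting for a mediator**

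Assume complication risk p1 = 10% with technique A and p0 = 20% with technique B, complication hazard ratio k = 2 or 3, and no other effect of technique. At time zero the hazard ratio for technique is

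HR = [(1 − p1) + p1·k] / [(1 − p0) + p0·k]

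- k = 2: (0.90 + 0.20) / (0.80 + 0.40) = 1.10 / 1.20 = 0.92
- k = 3: (0.90 + 0.30) / (0.80 + 0.60) = 1.20 / 1.40 = 0.86

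Cox models were fitted to simulated data (10,000 patients per replicate, 30 replicates, baseline hazard 0.05 per year, censoring at 5 years):

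| k | Technique HR, complication not in model | Technique HR, complication in model |
|---|---|---|
| 2 | 0.93 | 1.00 |
| 3 | 0.87 | 1.00 |

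The simulated values agree with the formula. In this deliberately simple case the whole technique effect disappears on adjustment.

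**3. Adjuvant therapy, if entered as a fixed covariate from first treatment**

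Assume no true effect, half the patients intended for therapy, and constant hazard λ. A patient counts as completed only if event-free at t0. Write S = exp(−λ·t0), E = five-year event-free proportion, r = 1 − E.

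- Completed group rate: (S − E) / [S·t0 + (S − E)/λ]
- Other group rate: [r + (1 − S)] / [r/λ + (1 − S)/λ − t0·S]

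Example with r = 25%: λ = −ln(0.75)/5 = 0.0575 per year.

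- t0 = 3 months: S = 0.9857. The rates are 0.0543 and 0.0608, ratio 0.89.
- t0 = 1 month: S = 0.9952. The rates are 0.0564 and 0.0586, ratio 0.96.

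Simulated Cox models with five-year event rates of 15% to 35% gave 0.94 to 0.98 at 1 month and 0.89 to 0.91 at 3 months. The formula gives about 0.96 and 0.89 to 0.90 over the same range. The wider simulated spread at 1 month comes from only 20 replicates per setting.

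**The case against.** The strongest reply is that the sentence has two aims. For examining risk factors, postoperative predictors such as pathological stage, R status and complications are legitimate, and the article does not say in so many words that one covariate set will serve every Table 1 contrast. The first part stands: these variables belong in a prognostic model. It does not rescue the sentence, because the reason given for including them is confounding, and no other adjusted time-to-event method is offered for items 4 to 8.

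Three stronger readings are tempting, and the documents do not support them.

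- A reader might infer that immortal time is built into the analysis. It is not. Adjuvant therapy is never named as a Cox covariate, item 33 is a data-entry definition, and landmark or time-dependent handling may be set out in an analysis plan that is not shown. The length of a course is not given either; because only one is required, the window may be short. The bias would fall mainly on the adjuvant coefficient, reaching technique coefficients only so far as the two are associated.
- A reader might infer that technique effects are usually pulled towards no difference. That fits a simple mediator, as in the illustration. Stage migration can work the other way: if wider dissection upstages patients, it may look better within each pathological stage. Collider bias can go in either direction.
- A reader might infer that nothing measured after surgery may ever be adjusted for. Pathological T, histological type and tumour diameter mostly describe disease that was there beforehand, and relying on clinical staging alone can leave residual confounding.

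**Conclusion.** The point holds for the stated rationale and covariate scope of the Cox model when it is used for the long-term technique, surgeon and anastomosis contrasts. Factors arising from the operation are not confounders of these contrasts, and adjusting for them can remove or distort the effect. The possible size is shown by a fully mediated hazard ratio of 0.93 or 0.87 that becomes about 1.00. This rests on assumed complication risks and hazard ratios and on technique having no direct effect, so it shows what can happen and does not forecast this cohort's result. The direction of bias in the real analysis cannot be fixed from the documents.

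The adjuvant-therapy issue is conditional: it arises only if the completed-course indicator enters as a fixed covariate from first treatment. Only secondary long-term analyses are affected. The wording should be corrected before those data are analysed, and there is time, since that analysis waits for five-year follow-up of all enrolled patients.

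**What to change.** Separate the two aims.

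1. **Technique, surgeon and anastomosis contrasts (Table 1, items 4 to 8).** Adjust the Cox model for pre-treatment variables only: age, ASA-PS, ECOG-PS, comorbidity, cT/cN, tumour location, timing of surgery and institution. Add a sensitivity analysis with pT, histological type and tumour diameter. Leave out 30-day complications, R status and node yield throughout, and leave pathological N out of the D-level contrast.
2. **Risk-factor aim.** Report a separate prognostic model that may include postoperative factors, and state that its technique coefficients are not to be read as causal effects.
3. **Adjuvant therapy.** If it enters the prognostic model, start follow-up at a fixed landmark (day 90, for example) or code it as time-dependent.

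The cost is mainly analysis-plan wording, since the covariates are already collected. A landmark drops earlier events from the prognostic model. Time-dependent coding needs the date on which therapy status changes, which the article does not list separately and which may have to come from the chart. Reliance on cT/cN may leave some residual confounding by true stage; the sensitivity analysis addresses this only in part.

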**Methods:**

Patients undergoing laparoscopic or robot-assisted surgery for right-sided colon cancer at participating institutions in the Laparoscopic Colorectal Resection Study Group will be prospectively enrolled between 3 July 2024 and 31 May 2026. This multicenter study expects to enroll a total of 2,000 colorectal cancer cases from 73 facilities nationwide. The primary endpoint is the incidence of postoperative complications classified as Clavien–Dindo grade ≥ III. Risk factors contributing to these severe complications will be analysed. As a key secondary endpoint, the incidence and predictors of intraoperative vascular injury near the superior mesenteric vein will also be evaluated.

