**Fig. 1 Fig1:**
[figure not shown]
Questionnaire regarding the preferred approach for conventional laparoscopic right colectomy**.** A nationwide questionnaire was conducted in 2023 by the Japan Society of Laparoscopic Colorectal Surgery. The most preferred approach in each institution is shown. According to the survey, the medial and retroperitoneal approaches are the most preferred

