
### Target number of cases

The target number of cases for the study is 2,000; nevertheless, we aim to recruit as many cases as possible within the study period.

The rationale for setting the target number of cases is described below.

The postoperative complication rate (grade ≥ III) of laparoscopic surgery in all patients with colon cancer in a Japanese randomised controlled trial (RCT) (JCOG0404) was 4.6% [3]. The postoperative complication rate (grade ≥ III) for laparoscopic CME of right colon cancer in a Norwegian RCT was 6.1% [10]. Based on these reports, we calculated that a sample size of approximately 2,000 cases is required to achieve a postoperative complication rate (grade ≥ III) of 5% and a 95% confidence interval within ± 1.0% based on the binomial distribution in this study.

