### Statistical analysis

The analysis of primary endpoints, key secondary endpoints, and other secondary endpoints regarding short-term outcomes will begin as soon as 120 days after the patient enrolment period ends. Long-term outcome analysis of the secondary endpoint shall be performed upon completion of the 5-year follow-up period for all enrolled subjects.

Primary/key secondary endpoints: Summary statistics of patient background and surgical outcomes will be calculated, and the proportion of major complications and intraoperative vascular injury around the SMV and their causes will be summarised. Logistic regression analysis will be performed using the factors listed in the survey items that may influence the rate of major complications and intraoperative vascular injury around the SMV. A random-effects model will be used to account for the differences between institutions. Patients who underwent open conversion before the lymph node dissection will be excluded from the analysis of key secondary endpoints, and the relationship between the extent and location of the damaged vessel and the magnitude of the effect on the perioperative period will be considered.

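### The Cox models for recurrence and late complications are stated without the institution effect that the plan gives its logistic and multiple regressions

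*Protocol article*

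**What the plan says.** All of this is in the protocol article.

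- **Primary and key secondary endpoints (Statistical analysis).** After the logistic regression: "A random-effects model will be used to account for the differences between institutions".
- **Secondary endpoints, general regressions (Statistical analysis).** After the multivariable logistic or multiple regression: "A random-effects model will be used to account for differences between the centres".
- **Secondary endpoints, subgroup comparisons (Statistical analysis).** After the subgroup logistic regression: "Multiple regression analysis will be used to analyse continuous variables. A random-effects model will be used to account for the differences between institutions".
- **Secondary endpoints, long-term outcomes (Statistical analysis).** The next sentences name Kaplan–Meier curves and then state that "a multivariate Cox regression analysis will be performed using preoperative and postoperative factors that may contribute to recurrence and late complications". No random effect, frailty, stratification or clustered variance is attached.
- **What is compared long term (Endpoints, Table 1).** Item 4 is "Long-term results by approach, robot or laparoscopy, and degree of dissection". Item 8 adds the anastomosis method.
- **How the exposures are distributed.** The legend of Fig. 1 says "The most preferred approach in each institution is shown", Fig. 2 does the same for robotic surgery, and the legend of Fig. 3 describes anastomosis preferences by institution.
- **Size (Abstract, Methods).** The study "expects to enroll a total of 2,000 colorectal cancer cases from 73 facilities nationwide".

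**The concern.** The plan accepts that institutions differ and adjusts for this in the logistic and multiple regressions, but the model for the long-term comparisons is stated without the adjustment. An ordinary Cox model treats patients of the same hospital as independent. Suppose patients in one hospital tend to receive the same technique and also share a raised or lowered hazard, through case mix, adjuvant practice or intensity of surveillance. The technique effect is then estimated partly from differences between hospitals, and the number of hospitals limits its precision more than the number of patients does. The model-based standard error misses this. Some long-term differences between techniques would then be declared significant at the plan's 0.05 level more often than that level implies.

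**Working it through.** **1. The plan's own figure.** The only computed figure is the target of about 2,000 for "a postoperative complication rate (grade ≥ III) of 5% and a 95% confidence interval within ± 1.0% based on the binomial distribution". The normal approximation gives n = 1.96² × 0.05 × 0.95 / 0.01² ≈ 1,825. The exact binomial interval has an average half-width of at most 1.0 point from about n = 1,940. The target therefore reproduces. It does not bear on the Cox models.

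**2. Inputs.**

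- From the document: 2,000 patients and 73 institutions, so 2,000/73 = 27.4 patients per institution. Significance level 0.05, taken as two-sided.
- Assumed, because the document gives no figure: an 18% event rate over five years (about 350 to 360 events), the frailty variance θ (how much the hazard differs between institutions), and the within-institution correlation r of the exposure (0 = evenly mixed everywhere, 1 = one choice per institution).
- Patients with pStage 0 or IV are not followed after discharge, so fewer than 2,000 enter these models. Events per institution drive the result, so a lower count is shown in step 3.

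**3. Approximation for an exposure fixed by institution, equal institution sizes.** Variance inflation = 1 + (events per institution) × θ. Actual type I error = 2 × [1 − Φ(1.96/√inflation)].

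| Events | Per institution | θ | Inflation | SE ratio | Type I error |
|---|---|---|---|---|---|
| 350 | 350/73 = 4.8 | 0.05 | 1.24 | 1.11 | 8% |
| 350 | 4.8 | 0.10 | 1.48 | 1.22 | 11% |
| 350 | 4.8 | 0.20 | 1.96 | 1.40 | 16% |
| 200 | 200/73 = 2.7 | 0.05 | 1.14 | 1.07 | 7% |
| 200 | 2.7 | 0.10 | 1.27 | 1.13 | 8% |
| 200 | 2.7 | 0.20 | 1.55 | 1.24 | 12% |

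**4. Simulation with partial clustering and unequal institution sizes.** An ordinary Cox model with one binary exposure of prevalence about one half, true log hazard ratio 0, gamma frailty, 73 institutions, 2,000 patients and 1,500 runs per setting. Each cell gives the ratio of true to reported standard error, with the coverage of the nominal 95% interval in brackets.

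| θ | r = 0 | r = 0.3 | r = 0.7 | r = 1 |
|---|---|---|---|---|
| 0 | 1.02 (95%) | 1.00 (95%) | 1.00 (95%) | 1.00 (96%) |
| 0.05 | 1.01 (95%) | 1.04 (94%) | 1.10 (92%) | 1.14 (92%) |
| 0.10 | 1.00 (95%) | 1.13 (92%) | 1.23 (89%) | 1.33 (86%) |
| 0.20 | 1.00 (95%) | 1.18 (90%) | 1.38 (83%) | 1.59 (79%) |

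The row θ = 0 and the column r = 0 show no deficit beyond simulation noise, so both kinds of clustering are needed.

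**5. Why the r = 1 column exceeds step 3.** The simulated institution sizes vary with a squared coefficient of variation of about 0.5, so events per institution, weighted by size, are about 4.8 × 1.5 = 7.2. Inflation becomes 1 + 7.2θ = 1.36, 1.72 and 2.44, with square roots 1.17, 1.31 and 1.56. These are close to the simulated 1.14, 1.33 and 1.59.

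**The case against.** The strongest reply is that the text is silent and does not exclude an institution term. This is a condensed article; a full protocol or analysis plan may specify a frailty, a stratified model or a clustered variance. The first random-effects sentence under the secondary endpoints could also be meant for all of them, survival included. The Discussion further argues that participating institutions are uniformly proficient, which would imply a small θ.

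Part of this stands. A reader might infer that the authors decided to leave institution out; the document does not support that. But the article states the adjustment three times, each time directly after logistic or multiple regression, and repeats it within the secondary-endpoint paragraph, which would be unnecessary if the first statement covered everything. The Cox sentence comes after the last of these and lists only patient-level and treatment factors in general terms. That is an inconsistency in the stated methods, beyond ordinary condensation. The proficiency argument did not stop the authors from using random effects elsewhere, and proficiency is not the only source of differing recurrence hazards.

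A second reply also stands: the legends do not show that all the compared exposures are hospital choices. They report the leading preference for approach and preferences for anastomosis, without within-hospital shares. Nothing is reported on dissection level or on how platform is chosen. The requirement of 10 prior robotic cases per institution makes some institutional dependence of platform plausible, but does not measure it. Anastomosis preference differs by platform, so hospitals using both may mix methods.

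**Conclusion.** The point holds as a conditional one. As stated, the Cox models lack the institution effect given to the logistic and multiple regressions. The intervals would be too narrow for exposures that cluster by institution, provided hazards also vary by institution. With about 350 events and θ from 0.05 to 0.20, the true standard error is 1.04 to 1.18 times the reported one at r = 0.3, and 1.14 to 1.59 times for an exposure fixed by institution. Event count, θ and r are all assumptions.

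Three stronger readings are tempting and not supported:

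- That the intervals will be too narrow for approach, platform and dissection level alike. The deficit vanishes if either kind of clustering is absent, and the document quantifies neither.
- That 2,000 patients are analysed as independent. The long-term models rest on fewer, given the stages without follow-up.
- That this undermines the study's only oncological evidence. R0 resection rate and lymph node harvest are also collected.

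The primary and key secondary analyses carry an explicit institution random effect and are untouched.

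**What to change.** Add one sentence to the long-term part of the Statistical analysis section: the Cox models include a shared frailty for institution, or use a sandwich variance clustered on institution. Name which one, because a frailty model estimates a hazard ratio within institutions and the sandwich keeps the population-average one. If the full protocol or analysis plan already says this, the article need only repeat it.

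No new data are needed, since the institution is known for every patient. The cost is somewhat wider intervals for clustered exposures. The long-term analysis waits for five years of follow-up, so the choice can still be fixed before those results are seen.
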